## **20 STUDY FINANCIAL AND ADMINISTRATIVE CONTEXT**

The Study Sponsor should ensure life and health insurance of the study subjects. In accordance with the applicable legislation, the subjects should be compensated for the damage in case of a threat to life and health associated with the use of the study/reference product.

## 22 APPENDIX 1. STUDY PROCEDURE SCHEDULE

|                                                                                                   |                               | Treatment period |         |             |         |             |         |             |                    |                         |
|---------------------------------------------------------------------------------------------------|-------------------------------|------------------|---------|-------------|---------|-------------|---------|-------------|--------------------|-------------------------|
| Visit                                                                                             | V1                            | V2               | V3      | V4
(TC*) | V5      | V6
(TC*) | V7      | V8
(TC*) | V9
EOT/E
T** | Unscheduled
visit*** |
| Day                                                                                               | Screening
-21 to
Day -1 | Day 1            | Day 7   | Day 28      | Day 56  | Day 84      | Day 112 | Day 140     | Day 168            | –                       |
| Week                                                                                              | W-3                           | W0               | W1      | W4          | W8      | W12         | W16     | W20         | W24                | –                       |
| Visit window                                                                                      | –                             | –                | ±2 days | ±3 days     | ±7 days | ±7 days     | ±7 days | ±7 days     | ±7 days            | –                       |
| Patient's informed consent                                                                        | X                             |                  |         |             |         |             |         |             |                    |                         |
| Evaluation of compliance
with inclusion/exclusion
criteria                                  | X                             |                  |         |             |         |             |         |             |                    |                         |
| Randomization                                                                                     |                               | X                |         |             |         |             |         |             |                    |                         |
| Demographics, life history                                                                        | X                             |                  |         |             |         |             |         |             |                    |                         |
| Medical history                                                                                   | X                             |                  |         |             |         |             |         |             |                    |                         |
| Height and body weight
measurement                                                 | X                 | X                | X       |             | X       |             | X       |             | X                  |                         |
| Physical examination                                                                              | X                             | X                | X       |             | X       |             | X       |             | X                  |                         |
| Evaluation of vital signs                                                                         | X                             | X                | X       |             | X       |             | X       |             | X                  |                         |
| Sweat test                                                                            | X                 |                  |         |             |         |             |         |             |                    |                         |
| DNA probe assay                                                                       | X                 |                  |         |             |         |             |         |             |                    |                         |
| ECG                                                                                               | X                             |                  |         |             |         |             |         |             | X                  |                         |
| Complete blood count                                                                              | X                             |                  |         |             | X       |             |         |             | X                  |                         |
| Biochemistry                                                                                      | X                             |                  |         |             | X       |             |         |             | X                  |                         |
| Serology (HIV, Hepatitis B
and C)                                                  | X                 |                  |         |             |         |             |         |             |                    |                         |
| Blood test for anti-drug
antibodies (IgG, IgE),
including neutralizing
antibody activity | X                             |                  |         |             | X       |             |         |             | X                  |                         |
| Urinalysis                                                                                        | X                             |                  |         |             |         |             |         |             | X                  |                         |
| Urine test for human
chorionic gonadotropin with
a test-strip                               | X                             |                  |         |             | X       |             |         |             | X                  |                         |

|                                                                                                             |                               | Treatment period |                |                |                |                |                |                |                    |                         |
|-------------------------------------------------------------------------------------------------------------|-------------------------------|------------------|----------------|----------------|----------------|----------------|----------------|----------------|--------------------|-------------------------|
| Visit                                                                                                       | V1                            | V2               | V3             | V4
(TC*)    | V5             | V6
(TC*)    | V7             | V8
(TC*)    | V9
EOT/E
T** | Unscheduled
visit*** |
| Day                                                                                                         | Screening
-21 to
Day -1 | Day 1            | Day 7          | Day 28         | Day 56         | Day 84         | Day 112        | Day 140        | Day 168            | –                       |
| Week                                                                                                        | W-3                           | W0               | W1             | W4             | W8             | W12            | W16            | W20            | W24                | –                       |
| Visit window                                                                                                | –                             | –                | ±2 days        | ±3 days        | ±7 days        | ±7 days        | ±7 days        | ±7 days        | ±7 days            | –                       |
| (for women with preserved childbearing potential)                                                           |                               |                  |                |                |                |                |                |                |                    |                         |
| Spirometry                                                                                                  | X                             |                  | X              |                | X              |                | X              |                | X                  |                         |
| Sputum sampling to study pharmacokinetics of the study/reference product                        |                               | X    |                |                |                |                |                |                |                    |                         |
| Assessment of clinical symptoms of chronic pulmonary disease exacerbation                                   |                               |                  | X              |                | X              |                | X              |                | X                  |                         |
| Interviewing the patient to assess clinical symptoms of chronic pulmonary disease exacerbation  |                               |                  |                | X  |                | X  |                | X  |                    |                         |
| Assessment of the quality of life according to the St. George's Respiratory Questionnaire, version 2.2      | X                             |                  |                |                |                |                |                |                | X                  |                         |
| Product inhalation                                                                              |                               | X    | X  | X  | X  | X  | X  | X  | X      |                         |
| Product dispensing                                                                                          |                               | X                | X              |                | X              |                | X              |                |                    |                         |
| Product return and accountability                                                                           |                               |                  | X              |                | X              |                | X              |                | X                  |                         |
| Handing over the patient diary                                                                              |                               | X                | X              |                | X              |                | X              |                |                    |                         |
| Returning and checking the patient diary                                                                    |                               |                  | X              |                | X              |                | X              |                | X                  |                         |
| Registration of the concomitant therapy                                                                     | X                             | X                | X              | X              | X              | X              | X              | X              | X                  |                         |
| Assessment of exclusion criteria                                                                            |                               |                  | X              |                | X              |                | X              |                |                    |                         |
| AE registration                                                                                             |                               |                  | X              | X              | X              | X              | X              | X              | X                  |                         |

 The height is measured once only at the Screening visit.

 The sweat test is performed at the Screening visit in the absence of documented confirmation of cystic fibrosis diagnosis. The sweat test procedure is described in Section 10.10.

 DNA probe assay to detect mutation in the CFTR gene is performed at the Screening Visit in the absence of documented confirmation of cystic fibrosis diagnosis (Section 10.11).

 The results of serological tests (HIV, hepatitis B and C) received no later than 30 days prior to the Screening Visit are acceptable.

 Sputum samples to study pharmacokinetic parameters of the study/reference product will be collected from patients having provided a consent for participation in the additional part of the study 1 hour  $\pm$  15 min before the inhalation of the study/reference product (after the patient's randomization), then 15 min  $\pm$  5 min after the end of inhalation of the study/reference product and 1 hour 45 min  $\pm$  15 min after the end of inhalation of the study/reference product.

 The list of questions for assessment of clinical symptoms of chronic pulmonary disease exacerbation asked by the clinical investigator or an employee of the study center authorized by him/her is presented in Section 10.6.

 Patients shall perform inhalations of the study/reference product at home, except for the patients who provided consent for participation in the additional part of the study for assessment of the DNase concentration in the sputum. These patients will receive an inhalation of the study/reference product at Visit 2 (Day 1) in hospital settings.

\*TC — telephone call.

\*\*EOT/ET — end of therapy visit / early termination visit.

\*\*\*During unscheduled visits, the required procedures, including laboratory and instrumental examinations, will be performed by the decision of the Investigator.

## 23 APPENDIX 2. QUESTIONNAIRE FOR PATIENTS

### St. George's Respiratory Questionnaire, v. 2.2 (\*)

Choose one answer for each statement:

**1. Over the past year, I have coughed:**

- Often
- Sometimes
- Rarely
- Once
- No

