### **10.14 St. George's Respiratory Questionnaire**

St. George's Respiratory Questionnaire (SGRQ), version 2.2, is intended to assess the quality of life of patients with chronic obstructive pulmonary diseases (APPENDIX 2). Filling out the self-administered Questionnaire takes a patient about 15 minutes.

The Questionnaire is composed of 76 questions grouped into 3 parts:

- Part 1 — Symptoms — to measure the degree of anxiety caused by respiratory symptoms.
- Part 2 — Activity — to measure restriction of movement and physical activity.
- Part 3 — Impacts — to assess the current psychosocial consequences of the bronchial obstruction.

In addition, a total score is calculated. The score is determined on the 100-point scale (the higher the value, the greater the impact of the disease is).

A change in the score of 4 points and more was considered clinically significant.

The Investigator will enter the Questionnaire data filled out by the patient at the Screening and on Day 168  $\pm$  7 days into the CRF.

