**2. Over the past year, I have brought up phlegm (sputum):**

- Often
- Sometimes
- Rarely
- Once
- No

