**3. Over the past year, I have had shortness of breath:**

- Often
- Sometimes
- Rarely
- Once
- No

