**4. Over the past year, I have had attacks of wheezing:**

- Often
- Sometimes
- Rarely
- Once
- No

**5. During the past year, how many severe or very bad unpleasant attacks of respiratory disease exacerbation have you had?**

- More than 3 attacks
- 3 attacks
- 2 attacks
- 1 attack
- None

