**2. Additional questions about your cough and breathlessness these days**

My cough hurts

My cough makes me tired

I get breathless when I talk

I get breathless when I bend over

My cough or breathing disturbs my sleep

I get exhausted easily

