**Scoring algorithm**

*Total*

Three component scores are calculated: symptoms, activity, impact. One Total score can be calculated.

*Principle of calculation*

Each Questionnaire response has a unique empirically derived value. The minimum possible value is zero, and the highest is 100.

*Each component of the questionnaire is scored separately in three steps.*

1. Sum up the values for all items with positive responses.
2. The values of missed items are deducted from the maximum possible value of each component. The values of all missed items are deducted from the maximum possible value of the Total score.
3. The score is calculated by dividing the summed values by the maximum possible weight for this component and expressing the result as a percentage:

$$\text{Score} = \frac{\text{Summed values of positive items in this component}}{\text{Sum of values of all items in this component}} \times 100$$

*The Total score is calculated in a similar way:*

$$\text{Score} = \frac{\text{Summed values of positive items in the Questionnaire}}{\text{Sum of values of all items in the Questionnaire}} \times 100$$

*Sum of maximum possible values for each component and Total:*

- Symptoms 662.5
- Activity 1,209.1
- Impact 2,117.8
- Total 3,989.4

(*Note:* The given values are the maximum possible values that could be obtained for the worst possible state of the patient.)

It should be noted that the Questionnaire requests a single response to questions 1–7, 9–10, and 17. If multiple responses are given to one of these questions, then calculate the average value acceptable for the positive responses to that question. We believe it is a better approach than losing the obtained data. This calculation technique was proposed and verified in our studies. Clearly, it is better to prevent such multiple responses from occurring, but it is difficult to completely prevent such occurrence. This method is used in the Excel calculator.

*Symptoms component*

It is calculated from the summed values of positive responses to questions 1–8.

*Activity component*

It is calculated from the summed values of positive responses to questions 11 and 15.

*Impact component*

It is calculated from the summed values of positive responses to questions 9–10, 12–14, and 16–17.

*TOTAL score*

The Total score is calculated by summing all positive responses in the Questionnaire and expressing the result as a percentage of the total value of the Questionnaire (as shown above).

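### The SGRQ Symptoms items look back over a year after only 24 weeks of treatment, so a true difference between products in the Symptoms change would be attenuated

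*Protocol*

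**What the plan says.** Protocol 10.14 and Appendix 1 schedule the SGRQ, version 2.2, twice: at Screening (Days -21 to -1) and at Visit 9 (Day 168 ± 7), which also serves as the early termination visit. Section 11.2 makes the change in the three subscale scores and in the Total a secondary endpoint. It serves objective 4, the comparison of quality of life between the products.

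Appendix 2 prints the form. The first five questions cover a year: "Over the past year, I have coughed", "Over the past year, I have brought up phlegm (sputum", "Over the past year, I have had shortness of breath", "Over the past year, I have had attacks of wheezing" and "During the past year, how many severe or very bad unpleasant attacks of respiratory disease exacerbation have you had". Question 6 asks how long the worst attack lasted and follows directly from question 5. Question 7 again names the past year. Question 8, on morning expectoration, gives no period. The scoring algorithm says of the Symptoms component: "It is calculated from the summed values of positive responses to questions 1–8".

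The other components differ. Numbering as the scoring algorithm does, questions 11–13 are framed in the present (question 12 is headed "Additional questions about your cough and breathlessness these days"). Questions 9 and 14–17 state no period. Question 10 asks about job loss without a time limit.

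Section 10.14 adds one general rule: "A change in the score of 4 points and more was considered clinically significant". It makes no exception for any subscale.

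**The concern.** Treatment starts on the day of randomisation and lasts 24 ± 1 weeks, so a year recalled at Visit 9 must reach back well before the first dose. Part of the Week 24 Symptoms score then describes a period that neither allocated product could have influenced, and part of that period was already reported at Screening.

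The direction matters in this trial. Section 15.2 says that the usual non-inferiority format is not feasible and tests a null hypothesis of equality instead. A non-significant result may therefore be read as similarity, and anything that shrinks a real difference favours that reading. Section 9.1 also indicates that some patients receive the reference product as part of standard care before entry. For them, the pre-randomisation part of the window can be reference-product time in either arm.

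**Working it through.** **Inputs.** Recall period: 365 days (Appendix 2, questions 1–5 and 7; question 6 by inheritance). First dose: Day 1 (5.5). Final form: Day 168, window 161–175 (9.8). Screening form: Day -21 to -1 (8.2). Component maxima: Symptoms 662.5, Activity 1,209.1, Impact 2,117.8, Total 3,989.4 (Appendix 2).

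**Checks on the plan's own figures.** 24 × 7 = 168 days. 662.5 + 1,209.1 + 2,117.8 = 3,989.4, which agrees with the stated Total.

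**Share of the recalled year before the first dose** = (365 − d)/365, with d the treatment days:

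| Visit 9 day | Days before first dose | Share before | Share on treatment |
|---|---|---|---|
| 161 | 204 | 55.9% | 44.1% |
| 168 | 197 | 54.0% | 46.0% |
| 175 | 190 | 52.1% | 47.9% |

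The share exceeds one half throughout the visit window. It is larger at an early termination visit.

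**Overlap of the two recalled years** = (365 − d − s)/365, with s the days from Screening to Day 1. The smallest value is (365 − 175 − 21)/365 = 46%. The largest is (365 − 161 − 1)/365 = 56%.

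**Can attacks fall in the pre-treatment part?** Exclusion criterion 2 bars exacerbations during Screening (up to 21 days) and in the 4 weeks before it. At Day 168 this leaves at least 197 − 21 − 28 = 148 recalled pre-treatment days in which attacks were allowed. An attack in that stretch still counts in question 5 at Week 24. If it was the worst of the year, it also fixes the answer to question 6. This does not depend on how patients average over time.

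**Possible size.** Let w be the weight that patients give to the on-treatment part of the year. The documents give no value for w. If the observed Symptoms difference is w times the true one, the true difference needed to show 4 points is 4/w:

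| w (assumption) | A true 4 points shows as | True difference needed to show 4 |
|---|---|---|
| 0.441–0.479 (even weighting, Day 161–175) | 1.8–1.9 | 9.1–8.3 |
| 0.460 (even weighting, Day 168) | 1.8 | 8.7 |
| 0.60 | 2.4 | 6.7 |
| 0.80 | 3.2 | 5.0 |
| 1.00 (only on-treatment weeks count) | 4.0 | 4.0 |

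The proportional form is itself an approximation. Questions 1–4 are ordinal, question 5 is capped at its top category, question 6 concerns a single attack and question 8 has no recall period.

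**Effect on the Total.** The Symptoms weight is 662.5/3,989.4 = 16.6%. With even weighting, a uniform 4-point change shows as 4 × (1 − 0.166 × 0.540) = 3.64, about 3.6 points.

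**The case against.** The strongest reply is that this is a limit on sensitivity, not a bias. A reader might infer that the Symptoms comparison is biased toward no difference in every case. The documents do not support that: if the products are equal, randomisation balances the recalled pre-study period in expectation, and there is nothing to distort. This part of the objection stands.

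A reader might also infer that the Total should be set aside because it contains Symptoms. With 16.6% of the weight and a shift from 4 to about 3.6 points under even weighting, that does not follow. Nor is it accurate that all of Activity and Impacts is anchored in the present. Only questions 11–13 are, and question 10 is open-ended history. What can be said is that no item in those components asks about the past year.

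Two further points have weight. Section 15.1 plans Wilcoxon and Mann–Whitney tests on score changes and contains no responder analysis or 4-point decision rule, so the threshold only guides interpretation. And on-treatment exacerbations are captured separately, by count and by time to event, with visit assessments, telephone questions and diaries. A difference in attacks does not rest on question 5 alone.

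These points limit the consequence but do not remove the mismatch. Objective 4 concerns quality of life, the Symptoms change is a named part of its endpoint, and the recall wording and visit timing are fixed in the Protocol. A later analysis plan cannot change what patients were asked.

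**Conclusion.** The point holds as a limit on one subscale of a secondary endpoint. Six of the eight Symptoms items state a one-year recall and a seventh inherits it. Within the Visit 9 window, 52–56% of that year precedes the first dose. These shares are date arithmetic and rest on no assumption beyond a 365-day year.

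The consequence is conditional: a true difference in symptoms would be attenuated, while equality would not be distorted. Even weighting (assumption) implies that 44–48% of a true difference shows and that roughly 8.3–9.1 points are needed to show 4. Heavier weight on recent weeks makes the loss smaller, and the documents give no basis for choosing a value. The Total is little affected, and the FEV1 primary endpoint is not affected at all.

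**What to change.** If questionnaires are not yet in use and an edition with a recall period inside 24 weeks is available (an assumption; the Protocol names none), use it at both visits. This costs a change of form.

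Otherwise amend 10.14, 11.2 and 15.1 as follows:

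- Rest the objective 4 conclusion on Activity, Impacts and the Total.
- Keep the Total as a comparative endpoint, with the recall limitation noted.
- Report the Symptoms change descriptively, as covering a recall year that is mostly pre-treatment.
- Do not apply the 4-point threshold to the Symptoms change.
- State that a lack of difference in Symptoms is not evidence of similarity.

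This needs wording only: no visits, patients or data are added. The downside is that Symptoms loses standing as a comparative endpoint. The Protocol Summary describes parts of the analysis in the past tense. If data have already been collected, changing the form is no longer possible, and the altered status of Symptoms should be declared as a later change and justified in the study report, as 15.3 requires for deviations from the analysis plan.
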